## Abstract

**Background:**

Chronic pain management is challenging for health systems worldwide. Clinical practice guidelines recommend interprofessional chronic pain management, but chronic pain clinics often have lengthy wait-lists. Advanced practice physiotherapists (APP) in orthopedic clinics and emergency departments have provided effective care and reduced wait times. The purpose of this study is to determine the feasibility of a clinical trial to evaluate the effects of integrating an APP into a chronic pain clinic setting. The primary objectives are as follows: (1) determine the feasibility of implementing trial methods by evaluating participant recruitment rates, retention, and assessment completion; (2) determine the feasibility of implementing the APP model of care by monitoring care provided and treatment fidelity; and (3) assess contextual factors that may influence implementation of the APP model of care by exploring the perspectives of patient participants and healthcare providers related to the model of care.

**Methods:**

This will be a single-arm feasibility study with embedded qualitative interviews to assess contextual factors influencing implementation by exploring participant and provider perspectives. Approximately 40 adults with chronic musculoskeletal pain referred for care at an interprofessional chronic pain clinic will be invited to participate in the feasibility study. Approximately 10–12 patient participants and 5–10 health professionals from the interprofessional team will be interviewed using an interpretive description approach. The APP model of care will involve participants seeing a physiotherapist as the first point of contact within the interprofessional team. The APP will complete an initial assessment and make care recommendations. Outcome measures planned for the full trial will be reported descriptively, including pain severity, pain interference, health-related quality of life, psychosocial risk factors for chronic pain, treatment satisfaction, perceived change, healthcare utilization, and healthcare costs over one year.

**Discussion:**

This study will inform plans to implement a full-scale study to evaluate the impact of an APP model of care in an interprofessional chronic pain management program. The results of the full study are intended to inform stakeholders considering this model to improve patient-centered and health system outcomes in interprofessional pain management program settings.

**Trial registration:**

ClinicalTrials.gov, NCT05336903 (Registered April 5, 2022).

**Supplementary Information:**

The online version contains supplementary material available at 10.1186/s40814-023-01352-9.

## Background

Chronic pain is a leading contributor to years lived with disability worldwide [1]. Direct and indirect costs associated with chronic pain are estimated at US $38.3 to US $40.4 billion per year in Canada, with musculoskeletal pain representing the majority of the costs [2]. Clinical practice guidelines recommend interprofessional chronic pain management based on high-quality evidence of effectiveness and cost-effectiveness [3–5]; however, access to interprofessional chronic pain management programs is a challenge for many individuals, with median wait times across Canada of over months duration [6–8]. This is in contrast to the quality standards for chronic pain management in Ontario, Canada, which indicate that people with chronic pain should receive an appointment with a chronic pain program within three months of referral [9].

Among individuals on waitlists for interprofessional chronic pain clinics, Choinière et al. found that almost two-thirds reported severe pain (≥ 7/10) that interferes with activities of daily living [10]. In addition, they found a high prevalence of both depression (50% of patients) and suicidal ideation (35% of patients) among individuals on waitlists for interprofessional chronic pain clinics. Waiting for chronic pain services is also costly to the health system, with reported median healthcare costs of US $1462 per month for those on waiting lists [11]. Given the personal suffering and healthcare costs incurred as individuals await chronic pain services, strategies to reduce waitlists and increase cost effectiveness are urgently needed to improve individual and societal outcomes of chronic pain.

One strategy that may contribute to the provision of guideline adherent care, while reducing waitlists, off-loading physician and nurse practitioner workload, and improving cost-effectiveness for people living with chronic pain, is incorporating an advanced practice physiotherapist (APP) into the interprofessional team. APP models of care involve physiotherapists (PTs) working to their full scope of practice using advanced knowledge, clinical reasoning skills, and experiences to help manage patients with complex conditions in an interprofessional team setting [12–16]. APP roles have been implemented in orthopedic care and emergency department settings, among other settings. For example, in an outpatient orthopedic clinic setting, APPs are commonly the first point of contact, triage patients appropriate for surgery, and refer to the surgeon when needed [14]. Research suggests that APP models of care in these settings can improve access and quality of care for patients with musculoskeletal conditions while maintaining safety and high levels of patient satisfaction [13–15, 17–19].

Musculoskeletal pain is the most prevalent classification of chronic pain [2] and among the most common reasons for seeking specialized health care for pain [20–22]. PTs have the competencies to complete a comprehensive assessment to identify physical, psychological, and social factors contributing to pain and disability among people with musculoskeletal pain and have successfully taken on advanced practice roles in other settings with musculoskeletal pain conditions [13]. Additionally, they have competencies in collaborative interprofessional care that will allow them to identify and engage the most appropriate team members in the care of people with chronic pain [23]. PTs may be well-suited to take on this first-contact role within the team for the subgroup of people with musculoskeletal pain seeking interprofessional pain care [1, 2].

APP models have yet to be implemented and evaluated in interprofessional chronic pain clinic settings; however, evidence from other healthcare settings suggests that this model of care has the potential to improve access to care while reducing costs. A review by Vedanayagam et al. [24] suggested that APP models of care can lead to improved access to care while maintaining a high degree of diagnostic accuracy, effective management, and similar patient health outcomes to usual care models across multiple settings. Another review of economic evaluations of APP models of care found that APP integration may result in reduced health system costs [25]. The potential mechanisms for cost reduction include the following: a reduction in referrals for surgery, APP salaries are less than physician salaries, and an attenuation of medications prescribed.

In order to successfully implement a full-scale trial to evaluate the effects of APPs working within chronic pain clinics, there are unique aspects of an interprofessional chronic pain clinic setting and patient population that need to be considered. There is the fundamental need to provide a comprehensive assessment and incorporate patient care within a wider interprofessional team with professionals with diverse training backgrounds and perspectives (e.g., social workers, psychologists, occupational therapists, nurse practitioners, anesthesiologists). Individuals with chronic pain often present with complex medical histories and higher rates of psychological and social factors related to pain that are likely to benefit from an interprofessional approach to care [26–28]. Integrating expertise from various disciplines is considered an effective approach to improve patient care for complex health conditions [29–31], and there is evidence that PTs can provide effective collaborative care [32–35].

Interventions with multiple components and care providers, such as a new APP model of care, introduce elements of complexity to the successful implementation of a full-scale clinical trial in an interprofessional chronic pain clinic setting. Some of these challenges include unique staffing arrangements, delivery of interventions in a dynamic setting, communication between healthcare providers (HCPs), recruitment of participants with competing priorities, and uncertainty around participant retention [36–38]. Medication discussion and management are often part of a comprehensive assessment and necessary treatment plan for individuals with chronic pain [39–41]. PTs in Canada are currently not able to prescribe medications, without medical directives, which may mean the APP model of care requires frequent involvement of physicians within the pain clinic, reducing the potential of the model to reduce physician workload.

Another rationale for this feasibility study is the need to understand contextual factors that may influence implementation within a fully powered trial. Several qualitative studies have been conducted related to the perceived barriers and facilitators of an APP model of care in other healthcare settings [42–46], but it is unknown how this model of care will be received by the patient participants and HCPs in a chronic pain clinic setting in the Canadian health system context. Themes related to APP knowledge, experience, and skills have been cited as drivers to the successful implementation of this model. A qualitative study in the Dutch healthcare system suggested that barriers related to a misalignment of physician values, a reluctancy to transfer care to APPs, and a lack of clarity of the value added from an APP model present significant challenges to the implementation of this model of care [47]. Being aware of these factors, as they relate to this feasibility study, will help inform a future full trial; perceived satisfaction and value from the model of care are vital to its uptake in a real-world setting.

Feasibility studies are often considered an essential prerequisite to large-scale studies that require a great deal of time, money, and resources [48]. The feasibility of an APP model of care needs to be tested in the chronic pain clinic setting to understand the perspectives of participants and their providers towards this model of care prior to conducting a fully powered clinical trial. The future aim of this line of research is to assess the impact of integrating an APP as the first point of contact within interprofessional chronic pain clinics. The primary objectives in a full trial will focus on participant health outcomes, care provided to participants, chronic pain clinic flow, the alignment of care with quality standards [9], and cost utility of the APP model in comparison to the usual physician- or nurse practitioner-led care. These objectives will be addressed in a full-scale clinical trial to be conducted following evidence of feasibility.

The aim of the current study is to evaluate the feasibility of conducting a future trial to evaluate the effects of implementing an APP role within a chronic pain clinic setting. The primary objectives of the feasibility study are as follows:To determine the feasibility of implementing the trial methods by evaluating participant recruitment rates, retention, and assessment completion over a 12-month periodTo determine the feasibility of implementing the new APP model of care by monitoring the care provided and treatment fidelityTo assess the contextual factors that may influence implementation of an APP-integrated model of care by exploring the perspectives of patient participants and healthcare providers.

## Methods

### Study design

This is a single-arm study where the focus is on testing the feasibility of the proposed full trial procedures [49]. Single-arm designs are considered appropriate where the goal of the study is to collect preliminary information regarding the feasibility and safety of a trial [50]. A feasibility, rather than a pilot, design is a pragmatic choice for the current study since the comparison arm, the usual physician- or nurse practitioner-led model, is already being used. The electronic surveys involved in the study can easily be integrated into a full trial across multiple clinical sites. Medical Research Council (MRC) guidelines for the development and evaluation of complex interventions have been used to guide this feasibility study [36, 37]. This study will collect data from participants with chronic pain and their providers to assess the feasibility of implementing and evaluating an APP role in an interprofessional chronic pain clinic setting. Both quantitative and qualitative data will be collected to assess the feasibility of the design (recruitment, data collection, retention), feasibility of intervention implementation (care provided, fidelity), and contextual factors that may influence implementation of the model of care (acceptability; barriers, facilitators, and strategies for refining the implementation; impact on the clinical process).

A SPIRIT checklist [51], modified for a feasibility study, has been completed and provided in Additional file 1.

### Setting

The Chronic Pain Clinic at Kingston Health Sciences Centre (KHSC) is located in Kingston, Ontario, Canada. The clinic is an interprofessional program that provides chronic pain management services to adult populations. The team includes five anesthesiologists, one neurosurgeon, four independently practicing nurse practitioners, three registered nurses, two PTs, two occupational therapists, one psychologist, and two social workers. The team is further supported by administrative staff and a research coordinator.

### Recruitment and consent

We will invite consecutive adult patient participants (18 years and older) with chronic musculoskeletal pain (> 3 months) referred to the KHSC Chronic Pain Clinic until we recruit approximately 40 patient participants. Forty participants were determined sufficient to address our feasibility outcomes using a practicality approach [51] and is within an acceptable rule of thumb range for pilot trials [52]. Potential participants will be triaged by a registered health professional from the Chronic Pain Clinic interprofessional team based on referral information and study inclusion/exclusion criteria. A registered practical nurse (RPN) will ask potential participants for consent to be contacted by a research team member. A research associate will then contact the potential participants to provide full information about the trial and invite them to participate. Consenting participants will then be enrolled in the study prior to completing the baseline assessment and scheduling an appointment with the APP.

### Inclusion and exclusion criteria

Inclusion criteria are as follows:Chronic musculoskeletal pain (pain > 3 months in duration) (e.g., neck pain, thoracic pain, limb pain, low back pain) -OR-Chronic widespread pain (e.g., fibromyalgia, myofascial syndrome) -AND-Eighteen years of age or older -AND-Must be able to read, write, and speak English.

Exclusion criteria as identified on referral package are as follows:Primary reason for referral stated as medication change or interventional pain management (e.g., injections, nerve block).Primary reason for referral is stated as headache or migraine.Reason for referral includes chronic pelvic pain.Referral indicates the individual has an untreated addiction, mental health disorder, or substance use disorder.Referral indicates cancer-related pain.Referral indicates medical “red flags” suggestive of non-musculoskeletal etiology of symptoms (e.g., unexplained symptoms, sudden weight loss, urinary retention, saddle anesthesia, evidence of upper motor neuron lesion, or fever).Referral states visceral pain or abdominal pain.

### Blinding and allocation concealment

Participants will be invited to participate in the study with an understanding that they will be assigned to either a model of care in which they see a physician or nurse practitioner first or a model of care in which they see an APP first, even though this is a single-arm feasibility study, and all participants will be assigned to the APP model of care. This partial masking at the time of consent and initial assessment was determined to be important to provide accurate estimates of feasibility (e.g., consent rate, percentage of consenting participants who see the physiotherapist first who also request to see the physician or nurse practitioner). Due to the nature of the intervention, patient participants and HCPs will not be blinded in the fully powered trial. Since the primary outcome measures are self-report measures (i.e., the participant is the assessor), the outcome assessor is similarly not planned to be blinded.

### APP role training

The core competencies informing the training of the APP were identified through a series of focus groups with an interprofessional panel of team members and patient participants using a nominal group technique and follow-up Delphi process (results not yet published) [53]. The PT recruited for the role in this feasibility study has several years of experience working with the Chronic Pain Clinic. To obtain the competencies for this role, the PT completed a training program outside of his normal responsibilities. The training included spending time shadowing, providing shared care, and practicing competencies with members of each profession from the interprofessional Chronic Pain Clinic team. The medical director of the Chronic Pain Clinic, one of the team members that frequently performs the initial assessment and development of the care plan, evaluated the PT on the competencies established through our focus groups (see competency checklist — Additional file 2). As a competency-based process, the training focused on the development of competencies, emphasized the abilities of the APP (not just knowledge), de-emphasized time-based training (allowing flexibility to achieve the competencies at different rates), and was learner centered [54]. As a competency-based training program, the training for the APP role was not meant to be standardized; rather, readiness to fulfill the APP role was assessed by the medical director.

### Usual care

Usual care at the KHSC Chronic Pain Clinic incorporates a physician- or nurse practitioner-led model, whereby patient participants are referred to the clinic to participate in an initial assessment by a physician or nurse practitioner who will make recommendations for the plan of care (e.g., urgent or emergent referrals for further investigation, medication management, referrals to allied HCPs, interventional procedures, or group-based treatments). Under this model of care, the physician or nurse practitioner may recommend the patient sees other members within the interprofessional Chronic Pain Clinic or as an outpatient in the community. While the physician or nurse practitioner collaborates with and draws on the expertise of the various members of the Chronic Pain Clinic team, they typically maintain the responsibility for directing and coordinating care until the patient is discharged from the Chronic Pain Clinic or a referral is made to another HCP to coordinate care.

### Intervention

The trained APP for chronic pain will provide an initial intake assessment, instead of the physician or nurse practitioner, and make care recommendations for patient participants, including what interprofessional team members will be involved in the participant’s care. In alignment with practice guidelines [55–57], the APP will approach the assessment with a biopsychosocial approach [29]. The assessment will include taking a thorough history; screening for pathologies contributing to pain; physical examination; using evidence-based screening tools to identify comorbid health conditions that require specific care (e.g., depression, addiction, post-traumatic stress); using validated tools to identify psychosocial risk factors associated with ongoing pain and disability; measuring pain severity and interference; and providing education on pain, prognosis, clinical processes, and team members. The APP will provide recommendations to the participant and healthcare team based on the assessment findings (e.g., urgent or emergent referrals for further investigation, medication management, referrals to allied HCPs, interventional procedures, or group-based treatments). Like the usual care model, the APP will collaborate with the wider team; however, the APP will maintain the overall responsibility for directing and coordinating the care until the participant is discharged from the Chronic Pain Clinic or a referral is made to another HCP to coordinate care. The APP will not be practicing in an extended scope role and, therefore, is fully autonomous and will not require delegation or transfer of responsibilities from a physician on the team.

### Evaluation and outcome measures

Participants will be asked to complete an online survey through a secure online data collection platform [Qualtrics, Provo, UT, USA [58]] to obtain baseline measures prior to their visit with the APP. Follow-up assessments will be collected electronically (or in person or by phone if requested by the participant) at 3, 6, 9, and 12 months after the initial assessment. If the participant does not complete the electronic survey, follow-up emails and phone calls will be made.

### Baseline measures

To describe the study population, the following data will be collected at baseline through the survey: age, gender, biological sex, education, identification as a member of a racialized group, identification as indigenous (First Nations, Inuit, Métis), duration and location of pain, comorbid conditions, current medications, work status, rurality, and annual household income. Comorbidities will be measured using the Self-Administered Comorbidity Questionnaire [59]; respondents select relevant comorbidities from a list of specific problems (with three optional, open-ended conditions), whether they receive treatment for the condition, and whether the problem limits their activities.

### Feasibility of trial design

#### Recruitment rate (patient participants/week)

The full trial will be deemed feasible, as planned, if we are able to recruit 40 participants over eight weeks (5/week). Additional sites or duration will be planned if this recruitment rate is not achieved.

#### Assessment completion

Given the longitudinal nature of this study, particular attention needs to be paid to the completeness of the outcome measures, in this case, completion of the surveys at each time point. We have determined that acceptable completeness will be satisfied if > 80% of all assessment items are completed across all follow-up time points.

#### Duration of survey completion

We will consider mean times for the completion of baseline and follow-up surveys of less than 60 min each to be acceptable. Completion times will be measured using the start and end times of the surveys.

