### Analysis

Descriptive statistics for all relevant baseline measures and outcomes will be reported, and decisions will be made regarding study feasibility based on the thresholds described under each feasibility outcome (e.g., < 20% attrition, > 80% of assessment items completed, and > 80% of items performed on the treatment fidelity checklist). Means (standard deviation) or medians (interquartile range) for continuous variables and frequencies (percent) for categorical variables will be presented. Quality indicator calculations are presented in the quality standards operationalization table (Additional file 4) and will be presented accordingly for each quality statement.

Health utilization measures will be presented as counts, and costs will first be calculated as the product of resource utilization and the corresponding unit cost. Summing these costs will provide the total costs and will be further assessed at each follow-up interval. The mean cost for the entire study period, as well as the mean cost for each time interval, will be presented.

We will document challenges in the collection and analysis of all data to inform the plan for the full trial where we intend to perform a complete assessment of adherence to quality standards and cost utility analysis.

The transcribed interviews will be analyzed using an interpretive description approach [61] to generate clinically relevant themes. Thematic analysis [63] will be performed by two investigators who will independently code the transcripts. As described by Braun and Clarke [63], the thematic analysis process will include familiarization with the data, production of initial codes, finding and reviewing potential themes, naming themes, and producing a report of the analysis. Identified themes will be used to describe patterns in patient participant and HCP responses to translate their perspectives into meaningful representations of the experience with the APP model of care as they relate to the acceptability of the APP role; barriers, facilitators, and strategies for refining model implementation; and perceived impact on clinical processes and outcomes.

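### Survey burden is judged on the mean of start-to-end times, so one very long interrupted survey could fail the 60-minute criterion (minor)

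*Protocol article*

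**What the plan says.** The section Duration of survey completion in the protocol article sets the criterion on an average. It begins "We will consider mean times for the completion of baseline and follow-up surveys", and the limit that it sets for every one of them is below 60 minutes. The next sentence defines the measurement: "Completion times will be measured using the start and end times of the surveys".

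Under Evaluation and outcome measures, the baseline survey is online: "Participants will be asked to complete an online survey through a secure online data collection platform". Follow-ups are due "at 3, 6, 9, and 12 months after the initial assessment", electronically unless the participant asks for an in-person or phone assessment. Non-completers are chased: "If the participant does not complete the electronic survey, follow-up emails and phone calls will be made".

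The Analysis section bases feasibility decisions on the threshold given under each outcome. It also lets the team present means with standard deviations "or medians (interquartile range) for continuous variables". That option concerns how results are presented. It does not move the survey-time threshold, which is stated as a mean. The article has no rule for pauses, resumed sessions or extreme times.

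**The concern.** The time between opening and finishing an online survey is not the same as time spent answering it. It includes any interruption, and the mean is the common summary most affected by one extreme value. Interruptions are plausible here. Respondents have chronic pain, the questionnaire set is long (several scales plus healthcare use, lost time and out-of-pocket costs), and reminders could lead someone to finish a survey that was opened earlier.

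What is at stake is a misleading answer on one feasibility criterion. The result could depend on whether a single person left a survey open overnight, not on how long the survey takes most people.

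**Working it through.** The 60-minute limit is a chosen cut-off and is not derived from other figures, so there is nothing to reproduce. The check is how far one record can move the mean.

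**Inputs**
- Limit: the mean must be below 60 minutes, so a mean of exactly 60 fails (Duration of survey completion).
- n = 40, from the plan to invite patients "until we recruit approximately 40 patient participants" (Recruitment and consent).
- n = 32 for a late follow-up, from 40 × 0.80, the edge of the under-20% limit (Attrition rate).
- Typical time m for everyone else: not in the article. Assumed range 20 to 55 minutes.

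**Formula.** If n − 1 people take m minutes and one record spans T minutes, the mean is ((n − 1)m + T)/n. It reaches 60 when T = 60n − (n − 1)m.

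**Worked case.** With n = 40 and m = 40, T = 2400 − 1560 = 840 minutes, or 14 hours. A 24-hour span gives (1560 + 1440)/40 = 75 minutes. The median is 40 in both cases.

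**Single span that brings the mean to 60**

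| Typical time m (assumed) | n = 40 | n = 32 |
|---|---|---|
| 20 min | 1620 min (27.0 h) | 1300 min (21.7 h) |
| 30 min | 1230 min (20.5 h) | 990 min (16.5 h) |
| 40 min | 840 min (14.0 h) | 680 min (11.3 h) |
| 50 min | 450 min (7.5 h) | 370 min (6.2 h) |
| 55 min | 255 min (4.25 h) | 215 min (3.6 h) |

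**What does not fail the rule.** One 1-hour pause adds 60/40 = 1.5 minutes to the mean. With m = 30 and n = 40, one 12-hour span gives (1170 + 720)/40 = 47.25 minutes, which passes.

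**Illustrative simulation** (all settings assumed: active time lognormal with mean 30 and SD 12 minutes, n = 40, each participant independently at risk of a 24-hour pause). With pause probabilities of 2%, 5% and 10%, the mean reached 60 in about 55%, 87% and 99% of runs. These figures nearly equal the chance that at least one person pauses (55%, 87% and 99%). The median reached 60 in none of the runs.

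All of this treats each time point separately. If the four follow-ups were pooled (up to 4 × 40 = 160 records), one record at m = 40 would need 9600 − 159 × 40 = 3240 minutes, or 54 hours.

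**The case against.** The strongest reply is that the problem needs an unusual record. The article does not say where surveys are completed, whether a session can be left and resumed, or how often that happens. Follow-ups may be done by phone or in person, and a research assistant instructs participants. A 14-hour entry among 40 would be obvious, the Analysis section allows a median to be shown, and the team undertakes to record data-collection difficulties. Rules for idle sessions are also detail that a fuller document may hold.

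Much of this stands, and it limits the size of the point. It does not remove the point, because the article itself fixes both the mean and the start-to-end measurement, and the decision rule refers back to that threshold. Setting aside a long record after seeing the data would be a post hoc choice.

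A reader might infer three stronger things that the article does not support:
- **That any pause can fail the survey.** The arithmetic needs a gap of many hours, unless typical times are already close to 60 minutes.
- **That a failed criterion would lead to outcome measures being dropped.** No action is attached to this criterion. By contrast, Recruitment rate and Care provided each state a response.
- **That the most burdened participants escape notice because they never finish.** Non-completion is mainly handled by separate criteria: more than 80% of items completed across follow-ups (Assessment completion) and under 20% attrition at 12 months (Attrition rate).

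**Conclusion.** The concern holds as a minor weakness in how one criterion is specified. With 40 respondents and an assumed typical time of 30 to 50 minutes, one survey spanning 20.5 down to 7.5 hours makes the mean reach the limit while every other respondent is inside it. With 32 respondents the range is 16.5 down to 6.2 hours. The conclusion rests on three things outside the article: the typical time, the possibility that a session stays open that long, and each time point being judged separately. How often such sessions would occur cannot be estimated from the article, so the simulated percentages only illustrate the mechanism. Survey time is one of several feasibility criteria and is not named among the primary objectives.

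**What to change.** Under Duration of survey completion, set the threshold on the median: median elapsed time below 60 minutes at each time point. Report with it the interquartile range and the proportion of respondents finishing within 60 minutes, and keep the mean as a descriptive figure.

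The cost is about one sentence. The start and end times are already to be collected, so no new data or platform feature is needed. There is one small downside: a median can pass with nearly half of participants over 60 minutes. The proportion finishing within 60 minutes is reported beside it for that reason.
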